### Inclusion and exclusion criteria

The inclusion and exclusion criteria of this study are in line with other ET-DBS studies as well as with the recommendations of the German DBS study group, which will help to ensure comparability [7]. Medication refractory ET is defined as at least two medical treatment attempts with at least two different medication groups (e.g., beta blockers, antiepileptic drugs) without a satisfying effect (either due to insufficient effect or side effects) for the patient.

In detail, the key inclusion criteria are:Confirmed diagnosis of ET according to the Movement Disorder Society (MDS) consensus diagnostic criteria [26]Age >18 yearsSufficient competence in the German languageAt least two medication attempts without satisfactory tremor controlCapability to provide informed consent.

Exclusion criteria are:Clinically relevant dementia that might interfere with the studyClinically relevant psychiatric disorder that might interfere with the studySurgical contraindication for bilateral DBSParticipation in another interventional trialBrain atrophy (i.e., width of third ventricle >10 mm)Preoperative and perioperative intake of anticoagulative medication.

### Outcome measures

The primary endpoint of this study is the reduction of tremor, measured via a reduction in TRS scores, due to PSA-DBS over 2 months compared to preoperative baseline. The TRS is a widely used and well-accepted scale for the clinical assessment of tremor and has been used in most controlled ET studies. The scale was first published in 1993 [24] and validated for ET in 2007 [27]. It consists of three parts: (A) tremor assessment, (B) task assessment, e.g., pouring water from one glass into another, writing, drawing spirals, and (C) a questionnaire assessing activities of daily living, e.g., eating soup with a spoon, social distress, hygiene; the different parts reflect the impairment due to tremor in different dimensions. The TRS has also been used as the primary endpoint measure in the retrospective analysis of Blomstedt et al. [13], which is the basis of power calculation for our study.

Secondary endpoints comprise general (SF-36 [25]) and disease-specific quality of life (QUEST [4], non-validated German version), depression (Beck Depression Inventory, BDI-II [28]), ataxia (International Cooperative Ataxia Rating Scale, ICARS [29]), and the patients’ and physicians’ subjective impressions on tremor severity and side effects (gait and speech) measured via visual analog scale (VAS). Stimulation-induced side effects are determined and recorded as adverse events throughout the study.

In addition, the amount of electric current applied during adjusted stimulation comprises a further endpoint. In case no difference in efficacy is seen between PSA and VIM stimulation in the crossover phase, it is particularly important to detect whether PSA stimulation requires less current on average and if the side effect profile differs in contrast to VIM stimulation. An acoustic speech sample is collected at each visit. The samples are analyzed by a phonetician and speech therapist as previously described [10, 30].

Together, these instruments provide a comprehensive assessment of subjective and objective treatment effects beyond mere motor effect.

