### DBS programming

Directly after implantation and until 7MFU the activated electrode contact is determined by the study protocol (ICL, PSA, VIM or ICL, VIM, PSA), but the parameters can be freely chosen in terms of amplitude, frequency, and pulse width. However, all patients must be stimulated with constant current (mA), with a positive case and a single active cathode. In the crossover phase, at each programming visit, a monopolar review from 0 to 5 mA in 0.5-mA increments is performed. The amplitude with the best effect and fewest side effects is chosen for the final setting and is usually further adapted by the investigator during the programming visit before discharge. In general, a monopolar configuration with 60 μs and 130 Hz is chosen initially. In case a patient does not present a sufficient effect, the frequency and pulse width can be additionally modulated to improve the outcome.

If stimulation on a certain contact does not lead to a sufficient effect or intolerable side effects occur, and thus a change of the electrode contact or electrode configuration is inevitable, the corresponding crossover phase cannot be continued for ethical reasons. In this case the EV of the respective crossover phase must be performed immediately. After the end of the crossover phase, at 7MFU, the activated contact can be freely chosen.

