### Blinding

During the crossover phase the study is performed in a double-blinded design. To ensure that neither the patient nor the physician is aware of the stimulation site (PSA or VIM), during the blinded crossover phase, each patient is seen by a blinded and an unblinded investigator (the latter usually being a study nurse). The unblinded study nurse performs all DBS programming during that phase. The physician decides according to clinical impression whether the stimulation parameters need to be modified (e.g., increase or decrease of amplitude or modulation of pulse width or frequency). The stimulation parameters and especially the activated contact (VIM or PSA) are documented in a separate file not accessible by the blinded physician. The blinded physician will be unblinded after all case report form (CRF) documentation of the crossover phase has been completed.

For the preoperative versus postoperative comparison of tremor suppression, all patients are videotaped and analyzed by an independent rater. The patients wear surgical caps before and after implantation, so that the rater cannot deduce the time point of data collection (i.e., preoperative versus postoperative) from, e.g., scars or short hair after implantation.

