## Discussion

This study investigates the effects and side effects of deep brain stimulation of the PSA and — with the help of the randomized crossover — contrasts the outcome with that of VIM stimulation. Although this monocentric study will primarily serve as a pilot study for a larger, multicentric trial, we expect direct findings to improve treatment of future patients with ET, e.g., through a better understanding of the side effect profiles of the two target areas.

So far, results on PSA versus VIM stimulation are conflicting, and it is unclear whether the higher efficacy of PSA stimulation compared to VIM stimulation is sustained in the clinical setting when the amount of current and the amount and severity of stimulation-induced side effects might vary between the two target areas. Theoretically, the higher efficacy of PSA stimulation over VIM stimulation might potentially be neutralized by the use of stronger current in the VIM group or more frequent side effects in the PSA group, the latter limiting acceptable program settings in that target area.

Therefore, first, this study was designed such that patients are stimulated with constant current and not constant voltage to facilitate direct comparison of the amount of current (independent of the impedance of the electrode contacts) applied to the target area in both groups. Secondly, our study strongly focuses on stimulation-induced side effects in both target areas. If our study detects a lower rate of side effects in one of the two groups, this could relativize the result on tremor suppression. In fact, it might be the therapeutic window, which comprises effect and side effect, and not the mere amount of tremor suppression that is crucial for preference of one or the other target area. Thirdly, the required sample size for demonstrating non-inferiority of PSA-DBS compared to VIM-DBS is the same as that calculated to demonstrate superiority if the non-inferiority margin is set at a difference of 9 Essential Tremor Rating Scale (ETRS) points in favor of VIM-DBS (with the same values of standard deviation, alpha, and power and assuming a true difference of zero). Therefore, our study has an acceptable power to show approximate non-inferiority for the case that tremor suppression is similar with both treatments, but side effects are reduced under PSA stimulation.

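### Final mA alone cannot show which target requires less stimulation, because pulse width and frequency may differ between a patient's PSA and VIM periods

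*Protocol article*

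**What the plan says.** All references are to the protocol article.

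- **Outcome measures** adds stimulation current to the endpoints: "the amount of electric current applied during adjusted stimulation comprises a further endpoint". If efficacy does not differ in the crossover, "it is particularly important to detect whether PSA stimulation requires less current on average".
- **Discussion** gives the reason for constant current rather than constant voltage: "to facilitate direct comparison of the amount of current", with the qualification that the comparison then does not depend on contact impedance. **Study procedure** likewise says that current-controlled settings improve comparability.
- **DBS programming** fixes the active contact until 7 months, but "the parameters can be freely chosen in terms of amplitude, frequency, and pulse width". Constant-current mode, a positive case and one cathode are mandatory. The usual start is stated: "In general, a monopolar configuration with 60 μs and 130 Hz is chosen initially". It then continues: "In case a patient does not present a sufficient effect, the frequency and pulse width can be additionally modulated to improve the outcome".
- **Blinding** confirms that the physician's instructions during the crossover may include "increase or decrease of amplitude or modulation of pulse width or frequency".
- **Statistical analysis** compares secondary outcomes between targets by repeated measures analysis of variance. It mentions no restriction to, or adjustment for, pulse width or frequency.

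**The concern.** Current amplitude is one of three settings that determine how much stimulation is delivered. The article's case for comparing current deals with a fourth quantity, impedance, and constant-current mode does remove that. It does not deal with the other two settings, which stay open in the very periods being compared.

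The permission to change them is tied to response. Pulse width and frequency may be modulated when a patient's effect at the active contact is insufficient, so departures from the starting values could be more common at one target than at the other. Randomizing the order does not prevent this, because the adjustment comes after randomization and depends on how the target performs. A period term does not remove it either.

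At stake is the reading of one exploratory endpoint. If tremor scores turn out similar, the article wants to ask whether PSA needed less current. Study question 2 and the Discussion both name stronger current in the VIM as something that could mask a PSA advantage. An answer from final mA alone could mislead if pulse width or frequency differed between the two periods.

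**Working it through.** The article gives no expected value, standard deviation or power for the current endpoint, so there is no planned figure to reproduce. The check is whether mA orders two settings in the same way as delivered charge.

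**Inputs from the article (DBS programming):** usual starting values of 60 μs and 130 Hz; amplitude review up to 5 mA in steps of 0.5 mA.

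**Assumptions for illustration only:** amplitudes of 2.0, 2.5 and 3.0 mA; alternative pulse width 90 μs; alternative frequency 180 Hz. None of these is a value from the article.

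**Formulas:** charge per pulse = amplitude × pulse width. Charge per second = amplitude × pulse width × frequency.

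**Reference:** 3.0 mA × 60 μs = 180 nC per pulse; 180 nC × 130 per second = 23.4 μC/s.

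| Setting | Current ratio | Charge per second | Charge ratio |
|---|---|---|---|
| 3.0 mA, 60 μs, 130 Hz | 1.00 | 23.4 μC/s | 1.00 |
| 3.0 mA, 90 μs, 130 Hz | 1.00 | 35.1 μC/s | 1.50 |
| 3.0 mA, 60 μs, 180 Hz | 1.00 | 32.4 μC/s | 1.38 |
| 2.5 mA, 60 μs, 130 Hz | 0.83 | 19.5 μC/s | 0.83 |
| 2.5 mA, 60 μs, 180 Hz | 0.83 | 27.0 μC/s | 1.15 |
| 2.5 mA, 90 μs, 130 Hz | 0.83 | 29.25 μC/s | 1.25 |
| 2.5 mA, 90 μs, 180 Hz | 0.83 | 40.5 μC/s | 1.73 |
| 2.0 mA, 90 μs, 130 Hz | 0.67 | 23.4 μC/s | 1.00 |

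Three results follow.

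1. At equal mA, one setting can deliver 38% to 50% more charge per second under these assumptions.
2. One step less current (2.5 against 3.0 mA) goes with a charge ratio anywhere from 0.83 to 1.73. The order reverses once the product of pulse width and frequency rises by more than 3.0/2.5 = 1.2.
3. When pulse width and frequency are the same in both periods, the current ratio equals the charge ratio, and mA is a sound comparison.

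**The case against.** **The article asks about current, and mA measures current.** This is correct as a description of the endpoint. The Discussion claims only independence from impedance, and constant-current mode delivers that. What remains is the word requires: saying that a target requires less current presumes that the other settings were held equal.

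**Programming follows a sequence.** There is a common usual start, then an amplitude review, and pulse width and frequency are brought in when effect is insufficient. If few patients leave the start, little is lost. This stands as a limit on size, and the article does not say how many will leave it.

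**The direction is not established.** A reader might infer that pulse width and frequency will be raised at the less efficient target, so that the mA comparison is biased towards no difference. The text does not support this. It says the settings can be modulated, without giving a direction, and nothing shows unequal use between targets.

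**Part of the answer is already planned.** Study procedure says that the stepwise current increase will inform the therapeutic window of each target, and a monopolar review takes place at each programming visit. This stands and should be credited. The gap is that the article does not say pulse width and frequency are the same in the two reviews, and the endpoint is tied to the adjusted setting.

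**Charge per second is not a proven measure of need.** It assumes that the three settings trade off linearly for clinical effect, which nothing in the article supports. This stands, and is why charge should accompany mA and not replace it.

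**The unseen full protocol or SAP may define the variable.** It may. The point rests on what the article itself states: the endpoint, the intended inference and the freedom in programming.

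**Conclusion.** The point holds in a limited form. Final mA cannot by itself show which target requires less stimulation unless pulse width and frequency match between a patient's two periods, and the article does not require them to match. The figures of 38% to 50% hidden charge, and of a reversal at one step less current, show what is possible under assumed settings; they are not estimates for this trial. The actual size and direction are unknown, and are zero if all patients stay at 60 μs and 130 Hz.

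A reader might also infer that the trial's fallback conclusion depends on this endpoint. It does not. The non-inferiority argument in the Discussion rests on similar tremor suppression with fewer side effects under PSA, not on current. The endpoint is a further one in a pilot whose comparison of the targets is largely exploratory, and the tremor-score analyses are untouched. The point is worth acting on because the article itself gives the question weight and the remedy is cheap.

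**What to change.** Change the analysis only; programming stays as it is.

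1. Keep final mA at the adjusted setting as the endpoint.
2. Report pulse width and frequency by target, including how many patients have different values in their two periods.
3. Add charge per second (amplitude × pulse width × frequency), averaged over the two sides, as a companion analysis. State that it assumes a linear trade-off between the settings.
4. Base any conclusion that PSA requires less current on within-patient comparisons at equal pulse width and frequency. Use patients whose final settings match, and the effect and side-effect thresholds in mA from the planned monopolar reviews where both were made at the same pulse width and frequency.

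The Blinding section says that stimulation parameters are documented in a separate file, so final settings need no new data collection. The cost is a few derived variables. The matched comparison may use fewer patients than the target recruitment of 15, so it should be reported with its own number and confidence interval.

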### Sample size and power calculation

Study question 1 concerns the tremor reduction at 5/7MFU due to PSA-DBS compared with baseline. Blomstedt [13] measured a mean reduction in TRS from 46.2 at baseline to 18.7 one year later in 21 patients with ET treated with PSA-DBS, with standard deviations of 10.1 and 8.8, respectively.

For study question 2 comparing PSA-DBS with VIM-DBS, a power of 80 % at significance level 5 % can be attained for a difference of 9 points on the TRS, corresponding to one-third of the tremor reduction from baseline due to PSA-DBS, with a sample size of *n* = 12 (calculated using the program PS version 3.0.43). A correlation coefficient of 0.5 between the two post-stimulation values is assumed.

For study question 1, testing for tremor reduction from baseline under PSA stimulation, assuming the same values of significance level and power, using the paired *t* test, the sample size was calculated as *n* = 4. Alternatively, with the previously determined sample size of *n* = 12 a tremor reduction of 9.7 points could be detected. This calculation involved assuming that the baseline and post-stimulation values of a particular patient are positively correlated, with a correlation coefficient of 0.5.

In case of missing data on the tremor score due to loss to follow-up or withdrawal of consent, the patient does not contribute to the analysis. A 20 % safety margin was allowed for such cases, giving a target recruitment of 15 patients.

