Only if implantation criteria are fulfilled, i.e., both leads are placed as described above and proper lead location is confirmed via stereotactic X-ray or postoperative CT scan, are patients included at 3MFU into the double-blinded, randomized phase of the study. Patients are randomized into two groups (group 1: VIM-DBS followed by PSA-DBS; group 2: PSA-DBS followed by VIM-DBS). The crossover is double-blinded (neither the patient nor the treating neurologist knows which area is stimulated in which period) and lasts for 4 months (2 months on each treatment). A programming visit (PV) is performed at the beginning of each period (at 3MFU and 5MFU) and the best clinical stimulation parameters of the respective contact are determined (i.e., best tremor suppression with no or tolerable side effects). The stepwise increase of current of the electrode contacts in the crossover phase yields a better understanding of the therapeutic windows (i.e., range between effect and side effect) of the two target areas. Double-blinding is also maintained during the programming visit, as adjustment of stimulation parameters is performed by an independent investigator (programmer) as instructed by the blinded rater. An evaluation visit (EV) is performed after each group (EV1 at 5MFU and EV2 at 7 MFU). As the effects and side effects are known to be immediate (although not systematically investigated for VIM-DBS), a longer washout phase between the two crossover phases is not necessary. After the crossover phase, the contact with the best effect and fewest side effects or more complex stimulation paradigms (such as double monopolar or bipolar configurations) can be freely chosen for further treatment until 12MFU.

For study question 1, the change from preoperative to postoperative TRS during 2 months of PSA stimulation will be analyzed. Therefore, the data will be pooled from the EV at 5MFU and 7MFU depending on randomization.

Patients without electrode placement according to the implantation criteria (see above) but with electrodes bilaterally located in the PSA will be stimulated in the PSA directly after implantation, evaluated at 3MFU and 12MFU, and will be excluded from the comparison between PSA and VIM. For the longitudinal PSA effect, 3MFU data from these patients will be pooled with 5MFU and 7MFU data from the randomization group, respectively.

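### The 9.7-point detectable reduction for study question 1 does not follow from the stated inputs, which give 8.5; the SD behind n = 12 for study question 2 is not stated

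*Protocol article*

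**What the plan says.** All figures are in the protocol article under Sample size and power calculation. The source study of PSA stimulation "measured a mean reduction in TRS from 46.2 at baseline to 18.7 one year later in 21 patients", "with standard deviations of 10.1 and 8.8, respectively".

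For study question 2 (PSA against VIM), "a power of 80 % at significance level 5 % can be attained" for a 9-point difference with n = 12. "A correlation coefficient of 0.5 between the two post-stimulation values is assumed". No SD is named for this comparison.

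For study question 1 (PSA against baseline, the primary endpoint), the section uses a paired t test, "assuming the same values of significance level and power", with a correlation of 0.5 between baseline and post-stimulation values. It gives n = 4, and adds that with n = 12 "a tremor reduction of 9.7 points could be detected".

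A 20 % margin for loss to follow-up or withdrawal of consent is then applied, "giving a target recruitment of 15 patients". Under Study procedure, only patients whose leads meet the implantation criteria enter the crossover. Those with bilateral PSA placement only "will be excluded from the comparison between PSA and VIM".

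**The concern.** Every input to the question 1 figure is stated except the sidedness of the test, so the figure should be reproducible. It is not, although n = 4 from the same inputs is. The 9.7 points are the article's statement of how sensitive the primary analysis is at the planned size.

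For question 2 a reader would naturally take the post-stimulation SD of 8.8 for both conditions, and that does not lead to n = 12. The missing SD matters in a second place. The Discussion claims acceptable power for non-inferiority at a 9-point margin, on the ground that the SD, alpha and power are the same as for superiority. That claim cannot be checked while the SD is unknown. The article also presents the study as a pilot for a larger multicentre trial, so its planning figures should be traceable.

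**Working it through.** **Inputs from the sample-size section:** means 46.2 and 18.7; SDs 10.1 (baseline) and 8.8 (post-stimulation); correlation 0.5 for each comparison; power 80 %; level 5 %. **Assumption:** two-sided testing, because sidedness is not stated. Power is from the noncentral t distribution with n − 1 degrees of freedom (df) and noncentrality (difference / SD of difference) × √n.

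**Question 1, SD of the change**

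√(10.1² + 8.8² − 2 × 0.5 × 10.1 × 8.8) = √(102.01 + 77.44 − 88.88) = √90.57 = 9.52

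**Question 1, the plan's n = 4.** The reduction is 46.2 − 18.7 = 27.5. Power is 95.7 % at n = 4 and 72.0 % at n = 3, so n = 4 reproduces and the method is the right one.

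**Question 1, the plan's 9.7 points at n = 12.** At 80 % power the detectable difference is 0.889 SDs: 0.889 × 9.52 = 8.46 points. This is 8.5, not 9.7 (9.7 / 8.46 = 1.15, so overstated by 15 %). Power at 9.7 points is 89.4 %.

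Variants tried at n = 12:

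| Variant | Detectable reduction |
|---|---|
| Stated inputs, two-sided | 8.46 |
| One-sided | 7.29 |
| Normal approximation | 7.70 |
| n − 2 df | 8.54 |
| SD of change 10.1 | 8.98 |
| 90 % power | 9.80 |

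None gives 9.7. The nearest, 90 % power, contradicts the stated power. To obtain 9.7 the SD of the change would have to be 9.7 / 0.889 = 10.9, which means a correlation of about 0.34 instead of 0.5.

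**Question 2, 9-point difference.** With a common SD s and correlation 0.5, the SD of the difference is √(s² + s² − s²) = s. So 8.8 in both conditions gives 8.8, and 10.1 gives 10.1. Mixing the two quoted SDs gives 9.52, as above.

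| SD of difference | Smallest n for 80 % | Power, n = 10 | Power, n = 11 | Power, n = 12 |
|---|---|---|---|---|
| 8.8 | 10 | 82.0 % | 86.3 % | 89.6 % |
| 9.52 | 11 | 75.9 % | 80.7 % | 84.6 % |
| 10.1 | 12 | 70.9 % | 75.9 % | 80.2 % |

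The planned analysis allows for a period effect, which costs one degree of freedom. With n − 2 df and SD 9.52, power is 79.7 % at n = 11 and 83.9 % at n = 12, so 12 is then the smallest n. Under n − 2 df, SD 10.1 gives 79.4 % at n = 12.

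**Margin.** 12 / (1 − 0.20) = 15 reproduces, and the 20 % loss uses the margin up. The documents give no rate of implantation failure. As an illustration only, if 15 counts patients before implantation and the full 20 % loss also occurs, 10 % failures leave 15 × 0.9 × 0.8 = 10.8 evaluable patients, and 20 % failures leave 15 × 0.8 × 0.8 = 9.6.

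**The case against.** **The 9.7 figure decides nothing.** It is offered as an alternative statement. The sample size comes from question 2, question 1 needs only 4 patients, and the expected reduction is 27.5 points. The error is also conservative. All of this stands and limits the weight of the point. It does not make the figure right.

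**The n = 12 may have a sound origin.** A reader might infer that 12 follows only if the baseline SD of 10.1 was put in for both post-stimulation values, and hence that the section uses two conflicting SDs. The documents do not support that. An SD of 9.52 with a period-adjusted model gives 12. So does 9.52 with n − 1 df, rounded up from 11 for two balanced sequences. With n − 1 df, any SD of the difference from about 9.6 to 10.1 gives 12. What remains is an unstated input, possibly given in the full protocol, and not a proven arithmetic error.

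**The margin may suffice.** A reader might infer that 15 recruits cannot yield 12 crossover completers. This is not shown either. No failure rate is given, the 20 % is a safety margin and not an expected loss, and the Statistical analysis section describes loss to follow-up as rare. Twelve remain whenever all losses together are three or fewer. If 15 means randomized patients, implantation failures do not touch it at all. Study procedure places implantation after enrollment, which suggests the other reading, but the sample-size section does not define the term.

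**Conclusion.** One figure is wrong as written: with the stated inputs and two-sided testing, n = 12 detects 8.5 points for question 1, and 9.7 points corresponds to about 89 % power. One-sided testing moves the answer further from 9.7. The error is conservative and changes no sample size.

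For question 2 the finding is a reporting gap. The only post-stimulation SD quoted gives n = 10 and about 90 % power at n = 12, so the stated 80 % implies a larger SD that the text does not name. It does not follow that the trial is undersized: with n − 1 df, n = 12 has 80 % to 90 % power under every SD that the quoted values yield, and in the period-adjusted model the lowest figure is 79.4 %.

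The remark on the margin is conditional. It applies only if the 15 are counted before implantation, and its size depends on a failure rate that the documents do not give.

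**What to change.** 1. Replace 9.7 with 8.5 points and state that the test is two-sided, if it is.
2. State the SD of the PSA-VIM difference used for n = 12 and the matching power: about 90 % with 8.8, 85 % with 9.52, 80 % with 10.1 (n − 1 df). Refer to the same SD in the non-inferiority statement in the Discussion.
3. Say whether 15 means enrolled or randomized patients. If enrolled, note that implantation failures come out of the same margin, and give the question 2 power at 10 and 11 evaluable patients: 82 % and 86 % with SD 8.8, 71 % and 76 % with SD 10.1.

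The cost is a few sentences in the sample-size section and a cross-reference in the Discussion. The design, the analysis and the recruitment target stay as they are.
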